### Criteria for dropout or early termination

#### Intervention Completion threshold.

Dropout will be considered if participants attend less than 27 sessions of a total of 36 sessions, being categorized as noncompliant, and will be included in an intention-to-treat analysis (ITT). ITT analysis will include all participants as randomized, regardless of the number of sessions attended, any treatment switches, lost to follow-up due to disease progression (including development of opportunistic infection), or second-line treatment or death. However, such participants will be excluded from the per-protocol analysis. Per-protocol analysis will be limited to participants who meet the adherence threshold, i.e., attending at least 27 sessions.

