#### Yoga program duration.

The 12-week, 36-session program is divided into two parts. The components of the yoga module are detailed in Table 2. The yoga therapist will supervise the 12-week program to ensure that participants learn asana, chanting, or meditation correctly and to prevent potential injuries. The Intervention schedule is detailed in Table 3. Although intervention will not be actively given after 12 weeks, patients will be encouraged to self-practice at home at least 3 times per week, and adherence to home practice will be monitored to assess sustained effects. For more detail, see S1 Annexure.

**Table 2 pone.0331992.t002:** Integrated Yoga Module for People Living with HIV (PLHIV).

Step	Practice	Rounds	Duration
1	Starting prayer	1	1 min
2	**Breathing Practices**	**–**	**–**
2A.	Hands stretch breathing	5	1 min
2B.	Hands in and out breathing	5	1 min
2C.	Straight leg raise breathing both legs	5	1 min
2D.	Salabhasana breathing and holding	5	1 min
3	**Loosening Exercises (Shithilikarana Vyayama)**	10 rounds each	10 min
3A.	Hand clench-Musthika Bandha	10	–
3B.	Wrist- Manibandha Naman and Chakra	10	–
3C.	Elbow -Kaponi Naman	10	–
3D.	Shoulder- Skanda Chalana	10	–
3E.	Neck-Griva Sanchalana	10	–
3F.	Knee-Janu Naman	10	–
3G.	Ankle- Goolf Naman and Chalna	10	–
3H.	Toes- Padasangula chalana	10	–
4	**Quick Relaxation Technique (QRT)**	1	5 min
5	**Asana**	1 round each	**–**
5A.	**Standing** – Ardhakati Cakrasana, Ardha Cakrasana and Padahastasana	1 round each	3 min
5B.	**Sitting-** Vakrasana **and** Janusirsasana	1 round each	2 min
5C.	**Balancing-** Vriksasana **and** Tadasana	1 round each	2 min
5D.	**Supine-** Veeparitakarani	1	1 min
6	**Pranayama**	–	–
6A.	Nadi Shuddhi	10	2 min
6B.	Ujjayi	9	2 min
6C.	Bhramari	9	2 min
7	**Deep relaxation technique (DRT)**	1	15 min
8	**Meditation**-Om Meditation	–	6 min
	**Total**	–	**60 min**

This table describes the structured sequence of the integrated yoga session, comprising breathing practices, loosening exercises, asanas, pranayama, relaxation techniques, and meditation.

Abbreviations: PLHIV = People living with HIV; QRT = Quick Relaxation Technique (QRT); DRT = Deep relaxation technique.

**Table 3 pone.0331992.t003:** Intervention schedule.

Total Contact Classes	12 contact sessions-3 sessions per week for 4 weeks
**Guided-online sessions**	24 online sessions −3 sessions per week for 8 weeks
**Total supervised yoga sessions**	36 sessions (including both contact and online sessions)

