### Compliance and adherence

To be compliant with the yoga intervention, every participant must attend at least 27 out of the 36 sessions (75%).

$$\text{Formula for compliance}=\frac{\text{No}.\text{ of session attended}}{\text{Total number of sessions offered }}*\text{1}\text{0}\text{0}$$

Adherence to yoga intervention is defined as a priori using both supervised session attendance and home-practice completion, details mentioned in Table 1.

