### Control group

The control group will be advised to continue standard medical treatment for the same duration, along with 12 weeks of moderate-to-intensity walking (prescribed brisk walk). The duration of prescribed brisk walk will be at least practiced for a duration of 60 minutes, 3 times/week, divided into three phases: 8-minutes warm-up, 20–25 minutes of brisk walking, and followed by a 15 minutes cool-down and supine rest. Providing moderate-to-intensity walking in the control arm is intended to ensure the candidates’ interest in continuing in the control arm, reduce attrition in the control group, and not limit them from potential risk-reduction practices. Both groups will be given a logbook to track their sleep, physical activity, and medication intake. For more details, see S1 Annexure.

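### The per-protocol threshold of 27 of 36 sessions is set for participants in general, but only the yoga arm has sessions to attend

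*Protocol article*

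**What the plan says.** The rule stands in the protocol article under Intervention Completion threshold: "Per-protocol analysis will be limited to participants who meet the adherence threshold, i.e., attending at least 27 sessions". The same paragraph uses the count to define dropout: "Dropout will be considered if participants attend less than 27 sessions of a total of 36 sessions, being categorized as noncompliant". Neither sentence names an arm.

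The threshold is introduced under Compliance and adherence as a yoga criterion: "To be compliant with the yoga intervention, every participant must attend at least 27 out of the 36 sessions (75"%). Table 3, under Yoga program duration, gives the total of supervised yoga sessions as "36 sessions (including both contact and online sessions"), made up of 12 contact and 24 online sessions.

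Under Control group, the walking regimen is described as follows: "The control group will be advised to continue standard medical treatment for the same duration, along with 12 weeks of moderate-to-intensity walking (prescribed brisk walk"). Its dose is given as "The duration of prescribed brisk walk will be at least practiced for a duration of 60 minutes, 3 times/week", and monitoring is by diary: "Both groups will be given a logbook to track their sleep, physical activity, and medication intake". The article describes no walking session to attend, no completion threshold for walkers and no exemption for them. It refers to S1 Annexure for more detail, and that annexure is not shown.

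The Intervention Completion threshold paragraph also removes from the per-protocol set, without regard to arm, participants who switch treatment, are lost because their disease progresses, move to second-line treatment or die. Under Statistical analysis, all analyses are to follow intention to treat.

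**The concern.** A per-protocol rule has to be applicable in both arms if it is to produce a between-arm comparison. This one is counted in a unit that one arm does not have. Someone will therefore have to supply a control rule later, possibly with data in hand, and the per-protocol estimate depends on which rule is chosen.

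The easiest repair, applying the count to yoga and leaving walkers out of it, is also the risky one. It compares yoga participants selected for persistence with walkers not selected in that way. If persistence goes with better 3-month HADS scores for any reason other than yoga itself, a difference appears without a treatment effect. Adjusting for the baseline score does not remove it. A per-protocol result that agrees with intention to treat is often read as support, and here the agreement could be partly an artefact. The labelling has the same defect: taken literally, every walker is a noncompliant dropout.

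**Working it through.** **Reproducing the plan's figures.** 12 contact + 24 online = 36 yoga sessions, and 27/36 = 75%, as stated. The design effect is 1.54/3.38 = 0.456. A two-sided t-test at 5% with 80% power then needs 76.6, so 77 per arm, as stated.

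**Which units each arm has.**

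| | Yoga | Walking |
|---|---|---|
| Prescribed occasions | 36 sessions (12 + 24) | 3 × 12 = 36 walks |
| Called sessions in the article | yes | no |
| Record | class attendance log | self-kept logbook |
| Completion threshold | 27 of 36 | none stated |
| Other per-protocol exclusions | apply | apply |

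The wording of the rule gives no way out. It speaks of an adherence threshold, but adherence too is defined for yoga alone: "Adherence to yoga intervention is defined as a priori using both supervised session attendance and home-practice completion".

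**Reading 1, literal.** A walker attends 0 of the 36 defined sessions and 0 < 27, so none of the 96 walkers qualifies. There is no comparator and no estimate.

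**Reading 2, walkers exempt from the count.** The other exclusions still act in both arms; only the attendance criterion is one-sided. Its effect when yoga has no true effect can be illustrated as follows.

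From the document: SD 3.38, and 77 per arm before the attendance filter. Assumed, because the document does not give them:
- p, the share of yoga participants reaching 27 sessions: 0.8
- r, the correlation of attendance with a lower 3-month HADS score given baseline: 0.2
- ρ, the correlation of baseline with 3-month score: 0.5
- per-protocol analysis by the same ANCOVA as the primary analysis

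Spurious difference = r × SD × √(1 − ρ²) × φ(z_p)/p, where φ(z_p) is the normal density at the cut that keeps a share p.

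- Residual SD = 3.38 × √0.75 = 2.927
- φ(z_p)/p = 0.280/0.8 = 0.350
- Difference = 0.2 × 2.927 × 0.350 = 0.205 points, or 0.205/1.54 = 13% of the design difference
- Standard error = 2.927 × √(1/61.6 + 1/77) = 0.500, with 77 × 0.8 = 61.6 left in the yoga arm
- Ratio = 0.205/0.500 = 0.41, so the two-sided rejection rate is Φ(0.41 − 1.96) + Φ(−0.41 − 1.96) ≈ 6.9%. Simulation of 20,000 null trials gave 7.1%.

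Range over the assumptions (r = 0.1 to 0.3, filter in the yoga arm only):

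| p | Spurious difference (points) | False-positive rate |
|---|---|---|
| 0.9 | 0.06–0.17 | 5.0–6.5% |
| 0.8 | 0.10–0.31 | 5.5–9.6% |
| 0.6 | 0.19–0.57 | 6.0–18.1% |

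If r has the opposite sign, for instance because more distressed participants attend more, the difference has the same size but goes against yoga.

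**Reading 3, matched rule.** Counting 27 of 36 walks applies the same 75% in both arms. In simulation the mean difference was then within 0.01 points and the false-positive rate 4.7–5.2%, provided that selection works alike in the two arms.

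**The case against.** The strongest reply is that this is a detail which a journal article may leave to the full protocol, the analysis plan or S1 Annexure. On that view the sensible reading is obvious: the walk mirrors yoga at three times a week for 12 weeks, so 27 of 36 walks is the natural counterpart, and no analyst would compare 96 participants with none. Part of this stands. The matched reading is the natural repair, and the annexure might contain it. It does not dispose of the point, because the article is not silent. It states a complete rule, fixed in sessions attended, and never calls walks sessions or says that they are attended.

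A second reply is that the per-protocol analysis carries little weight: everything is to follow intention to treat, and no model or supportive role is given for the per-protocol set. That is correct and limits the importance of the point.

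A reader might infer that exempting walkers would leave all 96 of them unfiltered. The documents do not support this: the exclusions for treatment switch, loss through disease progression, second-line treatment and death cover both arms. A reader might also infer that the per-protocol result will be biased toward yoga by a known amount. That is not supported either, since attendance, its link with outcome and the sign of that link are all assumed, and the 18.1% figure needs the two extreme assumptions together.

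**Conclusion.** The point holds for the per-protocol set and for the noncompliance and dropout labels. As written, the attendance rule cannot be applied to the walking arm: it either removes the comparator or selects on attendance in the yoga arm alone. It does not touch the intention-to-treat set, the primary ANCOVA or the sample size, and it is no ground for doubting the primary result.

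The first branch follows from the text with no assumption. The size of the second is illustrative: about 0.2 HADS points and about 7% false positives in the central case, close to nothing when attendance is high and weakly related to outcome, and larger if many yoga participants fall short. This is worth correcting, but as a secondary matter.

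**What to change.** Under Intervention Completion threshold, state the criterion by arm:
- yoga: at least 27 of 36 sessions in the class attendance log;
- walking: at least 27 of the 36 prescribed walks (3 × 12 weeks) in the logbook.

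Keep the other per-protocol exclusions for both arms. Reserve the term dropout for withdrawal or loss to follow-up, and call participants below 27 noncompliant. If no walking threshold is set, do not present a between-arm per-protocol comparison.

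The cost is a few sentences and an ethics-approved amendment. Walkers already record physical activity in the logbook, so at most a walk-count field is added. Recruitment was planned from March 2026 and may have started, but data collection is expected to run to March 2028, so the rule can still be fixed before any comparison of outcomes.

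The drawback is that walks are self-reported while yoga attendance is logged at the class. The two criteria match in dose but not in verification, so the near-zero bias of the matched rule is what one would hope for and is not guaranteed.

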#### Statistical analysis.

The normality of continuous outcomes will be assessed using graphical methods and the Shapiro–Wilk test. Continuous variables will be summarized as mean ± standard deviation (SD) for approximately normally distributed data or median (interquartile range [IQR]) for skewed distributions, and categorical variables as frequency (percentage).

The primary endpoint at 3 months will be analyzed using an ANCOVA model, with the 3-month outcome as the dependent variable, treatment group as the fixed effect, and baseline outcome value included as a covariate. This analysis will provide adjusted between-group mean differences with 95% confidence intervals. Effect sizes will be reported to quantify the magnitude of treatment effects. Secondary outcomes assessed at 3, 6, and 12 months will be analyzed as exploratory. Longitudinal analyses will be conducted using linear mixed-effects models with fixed effects for treatment, time, and treatment × time interaction, and baseline included as an adjustment covariate. Models will be estimated using restricted maximum likelihood (REML). An unstructured covariance matrix will be specified initially; if convergence fails, an AR (1) structure will be adopted. Degrees of freedom will be calculated using the Kenward–Roger method. Robust (sandwich) variance estimators will be applied if model assumptions are violated.

Medication adherence (ACTG questionnaire and self-reported) will be analyzed as a binary outcome using logistic regression. Multivariable logistic regression models will be used to identify independent predictors of adherence, adjusting for relevant demographic and clinical covariates.

All analyses will follow the intention-to-treat (ITT) principle. Missing data will be handled using multiple imputation under a missing-at-random (MAR) assumption. The imputation model will include treatment group, time, baseline and follow-up outcomes, relevant covariates, and treatment × time interactions. A sufficient number of imputations will be generated, and convergence will be assessed using standard diagnostics. Sensitivity analyses using delta-adjusted multiple imputation / pattern-mixture models will be conducted to assess robustness to departures from MAR.

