#### Description of the outcome measures.

The study will begin with a baseline screening visit, during which written informed consent will be obtained before starting any additional study activity. Clinical assessment, medical history, demographic characteristics, and questionnaire data will be collected at baseline and at the 3rd, 6th, and 12th-month follow-up visits. After being fully rested, all assessments will be conducted in the following order: heart rate, blood pressure, body composition, and questionnaires (Hospital Anxiety and Depression Scale (HADS), WHOQOL-HIV BREF, SF-36, Perceived Stress Scale, and the ACTG Adherence Baseline & Follow-Up Questionnaire). The primary endpoint is the change in anxiety and depression scores (HADS-A and HADS-D) from baseline to 3 months. All secondary endpoints will be assessed at baseline, 3 months, 6 months, and 12 months.

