### Sample size calculation

The sample size was determined based on a previous study, taking into account an expected mean difference of 1.54 and a pooled standard deviation of 3.38 [36]. The sample size is calculated for a two-sided independent-samples t-test to detect a standardized effect size (Cohen’s d) of 0.455, with a two-sided significance level α = 0.05, power 80%, and equal allocation (N₂/N₁ = 1). The required sample size is 154 participants (77 per group). After accounting for a 20% attrition rate, the adjusted sample size is 192 (96 participants per group).

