The present trial possesses several methodological strengths. It employs a randomized design to ensure balanced allocation between groups and to minimize allocation bias and predictability throughout the study. Assessments of outcomes are planned up to one-year post-randomization, enabling the evaluation of both immediate and sustained effects of the yoga intervention. The longer follow-up period will provide valuable insights into the durability of psychological and behavioral benefits over time. Additionally, the use of the TIDieR-Rehab (Template for Intervention Description and Replication for Rehabilitation) checklist ensures comprehensive documentation of the yoga intervention, thereby promoting clarity, transparency, and reproducibility of the study protocol.

A potential limitation of the trial lies in the reliance on self-reported measures for key outcomes such as depression, anxiety, stress, and quality of life. These subjective assessments may introduce recall or response bias; however, standardized and validated instruments will be used to mitigate these effects as far as possible.

If proven effective, the findings from this trial could mark a significant shift in HIV management from a primarily biomedical focus toward a more holistic, patient-centered approach that integrates mental health and overall well-being. Understanding the mechanistic physiological effect of yoga in the disease’s outcome may provide a strong rationale for systematically incorporating structured yoga practices into routine HIV care settings, ultimately enhancing both treatment adherence and quality of life among people living HIV.

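### The longitudinal model has one baseline slope for all visits, so its treatment × time contrasts are unadjusted for baseline; adding baseline × visit is a free, minor gain in precision for exploratory analyses

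*Protocol article*

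**What the plan says.** The Statistical analysis section describes two models for continuous outcomes.

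- The primary endpoint has its own single-visit ANCOVA, "with the 3-month outcome as the dependent variable, treatment group as the fixed effect, and baseline outcome value included as a covariate".
- Longitudinal analyses use a linear mixed model fitted by REML with "fixed effects for treatment, time, and treatment × time interaction, and baseline included as an adjustment covariate". For the covariance, "An unstructured covariance matrix will be specified initially; if convergence fails, an AR (1) structure will be adopted". Treatment × time is listed; baseline × time is not.

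The same section imputes missing data multiply and sets the status of the later results: "Secondary outcomes assessed at 3, 6, and 12 months will be analyzed as exploratory". Under Description of the outcome measures, "All secondary endpoints will be assessed at baseline, 3 months, 6 months, and 12 months". The Discussion counts the one-year follow-up as a strength, "enabling the evaluation of both immediate and sustained effects of the yoga intervention". The article does not say which estimate from the mixed model will be reported, the difference at each visit or the interaction contrast.

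**The concern.** A single baseline term assumes that the baseline score predicts the 12-month score as strongly as the 3-month score. Over visits at 3, 6 and 12 months, some weakening is plausible. Two things follow.

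- **Between visits.** The baseline term is the same at every visit and drops out of any difference between visits. If durability is judged by how the treatment effect changes from month 3 to month 12, the stated baseline adjustment contributes nothing to that estimate.
- **At each visit.** The shared slope is a compromise. If the correlation falls, it under-corrects at 3 months and over-corrects at 12 months. If HADS is also fitted longitudinally, the model's 3-month estimate can differ from the primary ANCOVA estimate even with complete data.

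What is at stake is precision in the exploratory longitudinal results.

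**Working it through.** **Inputs.** From Sample size calculation: "an expected mean difference of 1.54 and a pooled standard deviation of 3.38", 77 evaluable and 96 randomised per arm. Visit correlations are not in the documents and are assumed below. Time is taken as categorical, and the data as complete, as they are within each imputed data set.

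**The plan's own figure.** 1.54/3.38 = 0.456. A two-sided two-sample t-test at 5% with 80% power needs 76.6, so 77 per arm and 154 in total (power 80.2%). 154/0.80 = 192.5, against 192 stated. The figure reproduces and does not depend on the longitudinal model.

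**Why baseline cancels.** Let x̄ be an arm's baseline mean, ȳ_t its mean at visit t, and Δ the between-arm difference. With a common slope b, the effect at visit t is D_t = Δȳ_t − bΔx̄. Hence

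D_12 − D_3 = Δȳ_12 − Δȳ_3,

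whatever b is. With visit-specific slopes there is a further term −(b_12 − b_3)Δx̄. In 2,000 simulated data sets in each of two scenarios (77 per arm), the planned model's 12-minus-3-month contrast equalled the unadjusted difference in change to about 10⁻¹⁴.

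**Cost for the 12-minus-3-month contrast.** Let r_t be the correlation of baseline with visit t, and c that between the 3- and 12-month scores. In units of SD² × 2/n, the variance is 2(1 − c) with the common slope and 2(1 − c) − (r_3 − r_12)² with visit-specific slopes. With c = 0.5 the first is 1.

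| Assumed r at 3/6/12 months | (r_3 − r_12)² | Variance, visit-specific slopes | Ratio |
|---|---|---|---|
| 0.50/0.45/0.35 (mild) | 0.0225 | 0.9775 | 1.02 |
| 0.60/0.50/0.35 (moderate) | 0.0625 | 0.9375 | 1.07 |
| 0.70/0.50/0.30 (steep) | 0.1600 | 0.8400 | 1.19 |

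The moderate case is worth 192 × 0.0625 = 12 participants for this contrast. At 77 per arm and SD 3.38, the steep case gives an SE of 0.545 against 0.499; simulation gave 0.545 and 0.498. If r_3 = r_12 the ratio is exactly 1.

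**Cost at single visits.** The variance is proportional to 1 − r_t² + (r_t − b)² with the common slope and to 1 − r_t² with its own slope. Here b is the generalised-least-squares slope. The 3–6 and 6–12 month correlations are taken as 0.7, and the 3–12 month correlation as 0.6 (0.5 in the last row); the first row uses 0.6 throughout.

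| Assumed r at 3/6/12 months | b | Variance ratio at 3, 6, 12 months |
|---|---|---|
| 0.50/0.50/0.50 | 0.500 | 1.000, 1.000, 1.000 |
| 0.60/0.55/0.50 | 0.557 | 1.003, 1.000, 1.004 |
| 0.60/0.50/0.40 | 0.526 | 1.009, 1.001, 1.019 |
| 0.70/0.50/0.30 | 0.595 | 1.022, 1.012, 1.096 |

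For example, in the last row at 12 months: 0.91 + (0.30 − 0.595)² = 0.997, and 0.997/0.91 = 1.096. There the common slope gains almost nothing over no adjustment (0.997 against 1). In the third row most of the gain is already captured: from an unadjusted SE of 0.545, the planned model gives 0.438/0.472/0.504 and the extended model 0.436/0.472/0.499.

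**Chance imbalance.** With 96 per arm the SE of the baseline difference is √(2/96) = 0.144 SD, so a difference of at least 0.2 SD has about a 17% chance (z = 1.39). In the moderate case it moves the 12-minus-3-month contrast by (0.60 − 0.35) × 0.2 = 0.05 SD, or 0.17 points. The SE of that contrast is 3.38 × 0.144 = 0.49, so the shift is about a third of one SE. This is the same efficiency loss viewed conditionally on the imbalance.

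**The case against.** A reader might infer that the trial relies on the treatment × time contrasts, or that its results would be biased. The documents support neither. The primary inference is a separate 3-month ANCOVA with its own baseline slope. The 5% level is attached to the primary endpoint, the later analyses are labelled exploratory, and no hypothesis or research question concerns a change in effect between visits. The Discussion's remark on immediate and sustained effects reads at least as naturally as the difference at each visit, where adjustment still works. Simulated estimates were centred on the true value of zero under both models. A small disagreement between an exploratory model and the ANCOVA would leave no doubt about which is primary. All of this stands and limits the point.

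The size is also open: it rests on assumed correlations and may be zero. In the mild case, 2% of variance is about 1% of the SE. That stands too.

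The last objection is that a condensed article may leave a covariate-by-visit term to the full analysis plan, and that calling baseline a covariate does not exclude one. This carries some weight. But the section already fixes the fixed effects, estimation method, covariance structure and degrees-of-freedom method, and it names one interaction and not the other. As written, the model has a single slope, and that is what is assessed here.

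**Conclusion.** The point holds as a minor efficiency improvement. As listed, the model removes baseline adjustment from between-visit treatment contrasts and uses a slightly suboptimal slope at each visit. Under the assumed correlations, the variance of the 12-minus-3-month contrast is about 2%, 7% or 19% larger than needed for a mild, moderate or steep fall. Visit-specific effects lose about 0 to 2% under mild decay and about 10% at 12 months under steep decay. Nothing is lost if the baseline correlations are equal across visits. These figures assume complete data and an unstructured covariance; the cancellation itself needs only complete data and a common slope. There is no bias over repeated randomisation, and neither the primary ANCOVA nor the sample size of 192 is affected.

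**What to change.** In the Statistical analysis section, give the fixed effects for the repeatedly measured continuous outcomes as treatment, visit (categorical), treatment × visit, baseline and baseline × visit. Between-visit contrasts are then baseline-adjusted. With complete data and an unstructured covariance, the 3-month contrast matches the ANCOVA estimate for the same outcome.

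The cost is one model term, that is, two extra parameters. It needs no new data, participants or visits, and no change to the primary analysis. Data collection is expected to run to March 2028 and analysis follows completed follow-up, so the change can be made before any unblinded result exists.

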## Materials and methods

### Trial design

We propose a two-arm, parallel, prospective, randomized, open-label, blinded-endpoint trial with four assessment points: baseline, 3 months, 6 months, and 12 months. The study protocol has been developed in compliance with the Standard Protocol Items: Recommendations for Interventional Trials (SPIRIT) checklist (see S1 SPIRIT Checklist), and the SPIRIT schedule for the study is presented in Fig 1, including the screening, enrolment, and follow-up visit timelines [25]. The CONSORT flow diagram of the study protocol is shown in Fig 2. A visual abstract summarizing the study design is provided in Fig 3. The total study duration is 3 years, including 1 year of follow-up.

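### On its usual visit-order reading, the AR(1) fallback ignores the unequal 3- and 6-month gaps between follow-up visits; a fallback on actual months is a minor, free improvement

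*Protocol article*

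**What the plan says.** All from the protocol article.

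- **Schedule (Trial design):** "four assessment points: baseline, 3 months, 6 months, and 12 months".
- **Longitudinal model (Statistical analysis):** "linear mixed-effects models with fixed effects for treatment, time, and treatment × time interaction, and baseline included as an adjustment covariate". Baseline is a covariate, so the repeated outcomes are months 3, 6 and 12.
- **Covariance:** "An unstructured covariance matrix will be specified initially; if convergence fails, an AR (1) structure will be adopted". The text does not say whether AR(1) is indexed by visit order or by months elapsed.
- **Inference:** "Degrees of freedom will be calculated using the Kenward–Roger method", followed by "Robust (sandwich) variance estimators will be applied if model assumptions are violated". No criterion for a violation is given, and the sandwich is not tied to use of the fallback.
- **Status:** "Secondary outcomes assessed at 3, 6, and 12 months will be analyzed as exploratory". The primary analysis is separate: "The primary endpoint at 3 months will be analyzed using an ANCOVA model".
- **Missing data:** "Missing data will be handled using multiple imputation under a missing-at-random (MAR) assumption".

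**The concern.** AR(1) in its usual form counts steps between visits, not months. Months 3 and 6 are one step apart, and so are months 6 and 12, although the second gap is twice as long. If correlation fades with time, the 6-to-12-month pair is less correlated than the model allows and the 3-to-6-month pair more so. Model-based standard errors for changes in the treatment effect between neighbouring visits are then wrong, in opposite directions. The structure also holds the variance constant across visits.

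The Discussion presents one-year follow-up as a strength because it lets sustained effects be studied. What is at stake is how far to trust intervals for the change in effect between adjacent visits, and only if the fallback is reached.

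**Working it through.** **Inputs.** Visit times 3, 6 and 12 months (Trial design); unstructured first, AR(1) second (Statistical analysis). The protocol gives no correlation between visits, so a 3-month correlation *r* of 0.5 to 0.8 is an assumption. The protocol's only computed design figure, the sample size of 154 raised to 192, does not enter; it serves below only to judge whether the fallback would be needed.

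**Step 1: assumed truth.** Exponential decay with elapsed time and equal variances: corr(3,6) = r, corr(6,12) = r², corr(3,12) = r³.

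**Step 2: what visit-order AR(1) settles on.** The Gaussian likelihood was maximised over the AR(1) parameter and a common variance (large-sample limit). In each case the fitted parameter a equals the average of the two adjacent correlations, (r + r²)/2, and the variance is unchanged. For r = 0.7: (0.70 + 0.49)/2 = 0.595.

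**Step 3: standard-error ratios (model/true), balanced data.** A contrast between two visits has variance proportional to 1 − correlation, so

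- 6 vs 3 months: √[(1 − a)/(1 − r)]
- 12 vs 6 months: √[(1 − a)/(1 − r²)]
- 12 vs 3 months: √[(1 − a²)/(1 − r³)]

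The actual rejection rate of a nominal 5% test is 2[1 − Φ(1.96 × ratio)].

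| r | a | 6 vs 3 | 12 vs 6 | 12 vs 3 |
|---|---|---|---|---|
| 0.5 | 0.375 | 1.118 (2.8%) | 0.913 (7.4%) | 0.991 (5.2%) |
| 0.6 | 0.480 | 1.140 (2.5%) | 0.901 (7.7%) | 0.991 (5.2%) |
| 0.7 | 0.595 | 1.162 (2.3%) | 0.891 (8.1%) | 0.992 (5.2%) |
| 0.8 | 0.720 | 1.183 (2.0%) | 0.882 (8.4%) | 0.993 (5.2%) |

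Example, r = 0.8, 12 vs 6: √(0.28/0.36) = 0.882.

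The joint two-degree-of-freedom treatment × time test rejects 5.2 to 5.4%. The standard-error ratio for the 12-month arm difference is 1.00.

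**Step 4: a different truth.** With a constant correlation of 0.3 to 0.7, both adjacent contrasts are exactly right. The 12-versus-3-month standard error is 14 to 30% too large, because AR(1) imposes decay that is not there. That error is conservative and has nothing to do with spacing.

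**Step 5: unequal variances.** The model adjusts for baseline. If raw scores have equal variance and the same decay runs from baseline, a common baseline slope leaves a residual SD at 12 months 1.14 to 1.49 times that at 3 months. Equal-variance AR(1) then makes the 12-month arm-difference standard error 6 to 16% too small (rejects 6.4 to 9.8%) and the 12-versus-3-month one 3 to 6% too small (rejects 5.7 to 6.4%). This adds assumptions to those in Step 1 and is a sensitivity check, but it shows why the 1% figure needs equal variances.

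**Step 6: how likely is the fallback?** Three visits need 3 × 4/2 = 6 covariance parameters, with 154 to 192 participants. If the model is fitted to multiply imputed data, every participant has all three visits. Failure to converge is unlikely.

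**The case against.** The strongest reply has four parts.

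1. *The text does not fix visit-order indexing.* True. On a 3-month grid the visits are steps 1, 2 and 4, and AR(1) then gives r, r² and r³, with no error under Step 1. But AR(1) without qualification is usually read as visit order. If elapsed time is meant, the plan should say so, and the same edit settles it.
2. *The sandwich clause already covers this.* In part. A sandwich variance would correct the standard errors above. The clause depends on an undefined finding of violated assumptions, so it may not be used when the fallback is. Kenward–Roger adjusts a model-based covariance; the plan does not say which degrees of freedom go with the sandwich. With 154 to 192 participants that choice matters little.
3. *The direction of error rests on assumed decay.* This stands; Step 4 shows another pattern.
4. *The effect is remote and exploratory.* This stands too.

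A reader might go further and infer that the trial's test of whether benefit lasts to 12 months is invalid. The document does not support that. Treatment ends at 12 weeks, so 12 versus 3 months is the direct interaction contrast for durability, and it is within about 1% under equal variances. No section singles out 6 versus 3 or 12 versus 6 months as a test.

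**Conclusion.** The point holds as a minor weakness in the named fallback. The 9 to 12% understatement (12 vs 6 months) and 12 to 18% overstatement (6 vs 3 months) rest on five conditions together: the unstructured fit fails, AR(1) is indexed by visit order, correlation decays with elapsed time at an assumed 3-month value of 0.5 to 0.8, residual variances are equal, and model-based standard errors are reported. Nothing here touches the primary 3-month ANCOVA. The improvement is worth making because a fallback should suit the visit schedule, and because equal-step, equal-variance AR(1) can mislead under either pattern of correlation examined.

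**What to change.** Replace the fallback sentence with one stating that, if the unstructured fit does not converge, a continuous-time (spatial power or exponential) correlation on actual months will be used, with visit-specific variances if these can be estimated. State that any fallback fit will use a small-sample-corrected sandwich variance from the outset, without waiting for a judgement that assumptions are violated. Keep Kenward–Roger for the unstructured, model-based fit.

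Heterogeneous Toeplitz is not a suitable intermediate step. It also forces corr(3,6) = corr(6,12) and, under Step 1, leaves the 12-versus-6-month standard error 8 to 10% too small and the 6-versus-3-month one 10 to 16% too large. With 5 parameters against 6, it also offers little relief from non-convergence.

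The cost is a short edit to the statistical analysis section, with no extra data or budget. It can be made at any time before the analysis.
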